### Details of the intervention

FFE community partners funded the practice content areas. The amount of direct service was constrained by two things: 1) the desire to evaluate the effect of a small intervention on the use of existing service and 2) the realities of the funders’ budget. For these reasons, Family Recreation was funded for 1.4 hours per month per participant family, Family Healthy Lifestyle was funded for 3.5 hours per month, and Comprehensive was funded for 4.6 hours per month.

The practice content areas (recreation and family healthy lifestyle), practice principles (family-centredness, cultural sensitivity, capacity building, and reflection) and hours of direct service were essential elements of logic model development followed by request for proposals (RFP). The logic model elements formed the basis of an FFE RFP from interested community agencies.

Existing service providers in Edmonton were invited to submit a proposal for delivery of the FFE interventions. Evaluation of the proposals for service delivery led to the selection of a service delivery partnership of four community agencies called Families Matter. The Families Matter partners included: YMCA of Edmonton, Multicultural Health Brokers Co-operative, KARA Family Resource Centre, and Bent Arrow Traditional Healing Society. To achieve practice rigor Families Matter relied on: hiring practices that target selected front-line provider education and experience; in-service training directed at developing knowledge and behaviours believed to match the practice principles and content area selected; and supervision approaches.

Community-based intervention, when delivered in a research project, risks losing intervention fidelity for at least two reasons: (a) use of general practice principles and very broadly identified content area within which to practice, and (b) intervention drift [96]. In addition, there is a culturally based reluctance by service providers to submit to rigorous oversight of community developed practices.

For these reasons, action research methods were used to record and monitor the delivery of the service integration approaches. An administrative database was jointly developed to include qualitative and quantitative methods of recording practice to be used to calculate dose and to audit practices. In addition, the administrative and supervisory staff of Families Matter met weekly with the researchers to review and internalize the elements of the FFE service delivery logic model, which built the relationship and internalized the need for intervention fidelity. Similarly, a researcher spent half a day each week with the supervisors and family workers, focussing on trouble-shooting the practices associated with recording the practices in the data base and on the need for fidelity to the three service integration groups. Families Matter also assigned family workers and supervisors to only one service integration approach in order to support intervention fidelity. Lastly, focus groups and individual interviews were held, with supervisors and family workers, over the course of the 18 months of service delivery in order to specify the practices used in service integration. At the end of the project, a Service Integration Tool Kit was published [97].

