## Methods/Design

### Study design

FFE is a randomized, single-blind, longitudinal effectiveness trial with a 2 by 2 factorial design with three integration groups and a control group. The study was conducted in the City of Edmonton between January 2006 and August 2011. The study employed a multi-prong strategy to recruitment. Eligible families were invited to the study through five source programs for low-income families. In addition, posters and invitation packages were available at community agencies and through service workers. Information about the study was presented at community events where eligible families could inquire for more information. All families who received the source programs during the recruitment period were invited to participate in the study. Families were randomized after baseline data collection using a 1:1:1:1 allocation ratio. Those who were assigned to the intervention groups received between 18 and 24 months of service integration intervention. All families were followed by researchers for a total of three years with a minimum of ten interviews for data collection: two at baseline, and two at year 1, year 2, and year 3, respectively.

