### Primary analysis

The data will be analyzed using linear regression including terms for the healthy family lifestyle and family recreation service-integration approaches, their interaction and, where appropriate, time (a repeated measure). If the distribution of the primary outcome is right-skewed and cannot be transformed to a normal distribution, Poisson regression will be used. Estimates and corresponding 95% confidence intervals will be reported. The income group (Income Support vs. other source program) and the age of the focus child corresponding to strata variables in randomization will be included in the model.

Analysis of the FSI and quality of life data will be guided by the Canadian guidelines for the economic evaluation of health technologies [98], which comprises a five-part analysis. Part 1 will focus on identifying and describing the differences in use of social and health system services. Part 2 will result in the translation of these differences into dollar values, including the valuation of the intervention. Part 3 will focus on identifying and measuring the differences in quality of life for the children, parents and families. Part 4 will integrate the costing and quality of life information into a formal cost-utility analysis. Beginning with a budget impact analysis, Part 5 will examine the implications of the findings from an administrative and policy perspective.

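### Family workers each serve only one active approach, but neither the primary model nor the power calculation allows for worker clustering, so the intervals are too narrow if the worker ICC is positive

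*Protocol article*

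**What the plan says.** Randomisation is by family (Study design): "Families were randomized after baseline data collection using a 1:1:1:1 allocation ratio".

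Delivery is by people (Details of the intervention). A tender led to "selection of a service delivery partnership of four community agencies called Families Matter", and "Families Matter also assigned family workers and supervisors to only one service integration approach in order to support intervention fidelity". Funding is set per family: "Family Recreation was funded for 1.4 hours per month per participant family". The corresponding monthly figures for the other two active approaches are 3.5 hours (Healthy Lifestyle) and 4.6 hours (Comprehensive). The fourth arm, Existing Services, receives no service-integration worker from the trial.

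The model is described under Primary analysis as "linear regression including terms for the healthy family lifestyle and family recreation service-integration approaches, their interaction and, where appropriate, time (a repeated measure"), with income group and age of the focus child added as the stratification variables. Poisson regression is the alternative for a skewed outcome. Neither Primary analysis nor Other analyses names a worker, supervisor or agency term, a random effect for them, or a cluster-robust variance. The Sample size section gives no ICC or design effect.

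**The concern.** The intervention is a worker who connects families to services, and the primary outcome counts those connections. Differences in skill or style between workers could therefore show directly in the outcome. The article itself gives reasons to expect such differences: under Details of the intervention it describes general practice principles, very broad content areas, a risk of drift, and providers' reluctance to accept close oversight.

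Because each worker belongs to one approach, worker differences cannot be separated from the approach by comparing the same worker across arms. They have to be carried in the standard error. If they are not, an apparent effect of an approach may partly reflect a few unusually strong or weak workers. That matters because the article says the approaches were audited so that a successful one could be transferred elsewhere, where other workers would deliver it.

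**Working it through.** **1. The plan's own power.** Inputs from Sample size: 300 families per group, 25% attrition, alpha 0.05, f = 0.10 and 0.25. Analysed per group: 300 × 0.75 = 225, so N = 900. One-way ANOVA with independent families: noncentral F with 3 and 896 degrees of freedom, noncentrality f² × N.

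- f = 0.10: noncentrality 0.01 × 900 = 9, power 0.709 (stated 0.72).
- f = 0.25: noncentrality 0.0625 × 900 = 56.25, power above 0.999 (stated 0.99).

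The figure at f = 0.10 is the informative one. It is reproduced to within about one percentage point with no allowance for clustering.

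**2. Caseload (assumed).** The article gives no number of workers. Assume 100-130 direct service hours per worker per month and all of an arm's roughly 290 families carried at once. Caseload = hours ÷ funded hours per family; workers = 290 ÷ caseload.

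| Arm | Funded hours | Families per worker | Workers |
|---|---|---|---|
| Recreation | 1.4 | 100/1.4 = 71 to 130/1.4 = 93 | about 3-4 |
| Healthy Lifestyle | 3.5 | 100/3.5 = 29 to 130/3.5 = 37 | about 8-10 |
| Comprehensive | 4.6 | 100/4.6 = 22 to 130/4.6 = 28 | about 10-13 |

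**3. Variance inflation within an arm.** Observed fraction at 36 months (Losses and exclusions after randomization): 748/1168 = 0.64. With caseload m, DE = 1 + (0.64m − 1) × ICC. The ICC range 0.01-0.05 is assumed.

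- Recreation: 1 + (45.7 − 1) × 0.01 = 1.45 to 1 + (59.4 − 1) × 0.05 = 3.92.
- Healthy Lifestyle: 1 + (18.3 − 1) × 0.01 = 1.17 to 1 + (23.8 − 1) × 0.05 = 2.14.
- Comprehensive: 1 + (13.9 − 1) × 0.01 = 1.13 to 1 + (18.1 − 1) × 0.05 = 1.85.

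**4. Standard error of the contrast.** The planned intervals are for differences from an unclustered control arm, so the within-arm figure is not the one that matters. With equal arm sizes, the ratio of true to unadjusted standard error is √((1 + DE)/2), and the real two-sided error of a nominal 5% test is 2(1 − Φ(1.96/ratio)).

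| Arm versus Existing Services | SE ratio | Real error at nominal 0.05 |
|---|---|---|
| Recreation | 1.11-1.57 | 0.08-0.21 |
| Healthy Lifestyle | 1.04-1.25 | 0.06-0.12 |
| Comprehensive | 1.03-1.20 | 0.06-0.10 |

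**5. A check that does not use funded hours.** With a fixed 20 analysed families per worker in every active arm, simulation (4000 replicates, 225 per arm, no true effect) gives a rejection rate for the unadjusted four-group F test of 0.08, 0.10 and 0.20 at ICC 0.01, 0.02 and 0.05, against 0.049 at ICC 0.

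**The case against.** The strongest reply is that the article reads as a list of mean-model terms and is silent on variance estimation. A statistical analysis plan, not shown, could add a worker effect or robust standard errors. That is possible, and it is why the point asks for a change in the analysis and does not claim that the results will be wrong. But the model terms are set out explicitly, time is the only repeated structure named, and the power assumes independence. Followed as written, the plan makes no allowance.

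The second reply is that clustering is inferred. The article gives no caseloads, no rule of one worker per family, nothing on turnover, and no ICC. Teams or several workers per family are possible. This stands: the statement must be conditional on a positive ICC, and a strictly nested model may not fit how service was delivered.

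Third, services lasted 18-24 months, so at 36 months no family should still be receiving them and the correlation may have faded. This also stands; one ICC range for all visits is a simplification. In the other direction, the plan imputes by last observation carried forward, which would keep more families per worker than 64%. With the full caseload of 93 in Recreation and ICC 0.05, DE = 1 + (92.9 − 1) × 0.05 = 5.59 and the ratio is √(6.59/2) = 1.82.

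A reader might infer that the standard errors are definitely too small, or that the Recreation variance inflation of up to 3.9 describes the error in the reported intervals. The documents support neither: the first needs an ICC they do not give, and the second is a within-arm figure, not that of the contrast with control. Nor does the nesting by itself bias the point estimates.

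**Conclusion.** The point holds conditionally. The design is likely partially nested, and the stated analysis and power leave worker clustering out. For any positive worker ICC the intervals for intervention versus control are too narrow. How much cannot be taken from the documents. Under the assumptions shown, the understatement is slight for Healthy Lifestyle and Comprehensive at ICC 0.01 (3-4% at the lower caseloads) and considerable for Recreation at ICC 0.05 (up to about 57%). Recreation is the most exposed because its low funded hours imply few workers with large caseloads. If the ICC is close to zero, little changes. The matter deserves correction before the results are read as evidence about the approaches, but randomisation and outcome data collection are unaffected.

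**What to change.** - **Check the records first.** The article says "An administrative database was jointly developed to include qualitative and quantitative methods of recording practice to be used to calculate dose" and to audit practice. It does not say that worker identity was stored. Confirm that the records identify the worker or workers for each family.
- **If they do,** fit the primary model with a random worker effect in the three active arms only, treat control families as singletons, and use small-sample degrees of freedom. If families had several workers, use a multiple-membership model or a main-worker rule set in advance. Report the number of workers and the ICC per arm.
- **If worker identity is unavailable, or Recreation has too few workers to estimate the variance,** report the contrasts over a range of assumed ICCs and state that the intervals do not cover variation between workers.

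The cost is some data linkage and one added random effect. The intervals will be wider, most of all for Recreation.

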### Outcome measures

The study aimed to determine which of the interventions impact accessibility in the most efficient and effective manner. Where possible, the measures were selected because of their standardization, the presence of published norming data, and their utility as comparators to other studies of low-income families.

The primary outcome, family linkage to health and social services, was measured using an innovative tool, “Family Services Inventory” (FSI). This tool was developed by a health economist, in consultation with FFE researchers. The FSI adopts a societal perspective and measures public and private consequences for families. The FSI was developed to maximize precision while minimizing patient burden and recall bias. A FSI toolkit comprised in-service training materials for data collectors, a user manual, a codebook, and a calendar (a memory aid to reduce recall bias). Annual data capture of resource use during the prior month was conducted in face-to-face interviews. Due to variations in scheduling interviews, resource use is normalized to the observation period (time between first and second visit). Characteristics of services and data allowing for costing of services were also collected in the FSI.

An overview of measures associated with the primary, secondary and intervening outcomes is found in Table 1.

**Table 1 T1:** Outcomes, measures, and instruments

**Outcome**	**Measure**	**Instrument**
	**€ Primary Outcomes €**	
Linkages between low-income families and established services in their communities	Average number of times the family linked to services	Family Services Inventory (FSI)
Quality of life	Preference based measures	Visual Analogue Scale (EQ VAS) Australian Quality of Life (AQoL)
	**€ Secondary Outcomes €**	
Characteristics of linkages between families and services	Type of service, satisfaction	FSI
Costs to service systems	Costs of services linked to	FSI
Adult physical health	General health status	Single general health item from National Longitudinal Survey of Children and Youth (NLSCY), EQ-5D
Adult psychosocial health	Somatization, obsessive-compulsive, interpersonal sensitivity, depression, anxiety, hostility, phobic anxiety, paranoid ideation, psychoticism, self-esteem	Symptom Checklist (SCL-90-R), Self-Esteem Inventory
Linkages to community	(a) Perceived social functions and provisions obtained from relationships with others; (b) social and civic participation; (c) barriers to participation; (d) neighbourliness	(a) Social Provision Scale; (b) items from the Health and Participation survey; (c) Left Out survey; (d) items from NLSCY
Child physical health	General health status, chronic conditions, injuries, nutrition, sleep pattern, risk behavior	40 items from NLSCY
Child psychosocial health	Socio-emotional development, personality, behavioral problems, attitudes, mental health	Behavioral Assessment System for Children (BASC)
Child Achievement	Spelling, Arithmetic, Reading, Receptive Vocabulary	Wide Range Achievement Test; Peabody Pictorial Vocabulary III
Family Functioning	(a) Problem solving & communication skills, (b) parenting,	McMaster Family Assessment device
Socio-demographics	Ethnicity, immigration status, education, occupation, family type, level of income, source of income, security of housing, number of children, neighbourhood	Items from NLSCY

### Data collection and management

Data were collected at baseline, prior to randomization, and then every 12 months for three years. One adult respondent per family was selected based on familiarity with the children. A focus child was randomly selected (using computer-generated randomized lists stratified by number of eligible children) amongst the children within the household at screening. When appropriate, children’s data were collected from the focus child. During data collection phase, follow-up data collections were conducted annually for all families. Research assistants who had established rapport with families since first contact arranged each data collection. Data collectors, blind to the group assignment, collected data during home visits. FFE researchers adopted a professional human resource model with a data collection supervisor who oversaw 29 data collectors and 36 interpreters. We adopted this model because (a) a number of our instruments are standardized measures requiring psychometric assessment skills, and (b) it enhanced our ability to attract and retain a staff with adequate credentials and experience. Most of our data collectors had completed or were working toward their Master’s degrees in a variety of health and social science fields. Data collectors were required to work evening and weekends, to be responsive to the schedules of the families, and all were rigorously trained on the data collection process, crisis management, and cultural sensitivity. A detailed manual of operations was available to the research assistants and data collectors at the coordinating office. Due to the volume of the data collected and to avoid fatigue of the primary participants, each data collection point consisted of two visits approximately 28 days apart. The 28 days lapse also allowed for a prospective collection of the services accessed by the family.

All data were collected using standardized case report forms by trained data collectors and then faxed to the Epidemiology Coordinating and Research (EPICORE) Centre -- a clinical trials and health services research centre within University of Alberta, for data entry. EPICORE was responsible for data storage and quality assurance with the help of the data collection team. The database was coded in Microsoft Visual FoxPro V7.0. The use of free text fields and open-ended questions were eliminated from the forms, wherever possible. Simple (e.g., aberrant values, missing values) and complex verification rules were applied. Study subjects were identified by a unique study number assigned at time of enrolment. The study participants’ personal information was not included in the database. Confidential contact information and documents containing the link between the primary parent’s and focus child’s names and the assigned study number were stored in locked file cabinets at the FFE coordinating office. Sixty randomly sampled from the first 200 baseline data files (all forms in part 1 and 2) were audited. The transcription error rate was less than 1% (5 errors were identified).

### Randomization

The random allocation sequence was computer generated using R version 2.8.1 software.

We used permuted blocks of 8 and 12, stratified by type of income (Income Support receipts versus other source programs) and age of the focus child (0 to 3.9, 4 to 6.9, 7 to 9.9, 10 to 12.9 years).

### Allocation to experimental group and implementation

The intervention assignments were concealed on serially numbered, opaque, sealed envelopes. After the baseline data collection was completed, research assistants phoned the families and then opened randomization envelopes that were pre-stratified according to low-income status (i.e., receiving income supports vs. other source programs) and age of the Focus Child. Families were informed of their group assignment at that time. Research assistants explained the next steps to families. For those allotted to the intervention groups, their contact information was passed onto the service delivery workers. Research assistants explained to families that researchers would be in contact again for follow-ups, but families could contact them before then if they were moving or had any concerns about the study.

### Blinding

The data collectors and the investigators were blinded from the group assignments. The families, the service delivery workers and the research assistants were not blind to the group assignments at any point in the trial. Investigators were unblinded when the datasets were cleaned (January 2012).

### Sample size

Projecting a moderate (f = 0.25) and even a small (f = 0.10) intervention effect size (mean divided by standard deviation), given an alpha of 0.05 and a 25% attrition rate, the study proposed an initial sample size of 300 families per group to detect any significant difference between the four groups (power was 0.99 and 0.72, respectively). The study randomized approximately 290 families to each group. The overall alpha value was not controlled for multiple comparisons. No interim analyses were planned.

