### Aim of the study

This study focused on evaluating service integration approaches directed at increasing linkages between low-income families and services existing in their communities. The primary research question was:

What are the effects of three community-based service-integration approaches (Family Healthy Lifestyle, Family Recreation and Comprehensive), as compared to a control model (Existing Services), on the number of linkages that families initiate and maintain with established health and social services?

The design of the study enabled a thorough examination of several additional questions that are critical for understanding the influence of different service-delivery models on family linkages with established services, costs, and health. Secondary research questions included:

1. What are the relative effects of different service integration approaches on specific characteristics of family linkages to established service (e.g., type of service, satisfaction with), and how do the frequency and type of involvement change over time?

2. What are the costs to service systems of each of the service-integration approach over time?

3. What are the physical and psychosocial health outcomes of family members, over time, associated with each of these service integration approaches?

In order to effectively contribute to policy change, it was important to identify concurrent and antecedent variables related to linkage, cost, and health outcomes, and to estimate the likely impact of these variables [94,95]. Tertiary research questions included:

4. What is the intervening role of family functioning (family problem solving, communication, parenting, connections to community) between each of the four service integration approaches and linkage to services, cost, and health outcomes for family members, and how does this role change over time?

5. To what extent does sociodemographic profile (e.g., ethnicity, immigrant status, education, occupation, family type, level of income, sources of income, security of housing, number of children) influence the relation between each of the four service integration approaches and linkage to service, cost, and health outcomes, and how does this influence change over time?

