### Losses and exclusions after randomization

As indicated in Figure 1, during the process participants could either withdraw (i.e., lost to follow-up) or be ‘dormant’ for some of the data collection points (i.e. unavailable). At 36 months we were able to collect data from 748 families; data from 414 families were lost (135 Existing Services, 88 Family Recreation, 110 Family Healthy Lifestyle, and 91 Comprehensive). Table 2 shows reported reasons for withdrawal.

**Table 2 T2:** Losses and exclusions

**Reasons for withdrawal**	**Before randomized**	**After randomized**	**Reasons for withdraw (count)**
Not interest in	55	18	73
Too busy/No time	47	40	87
Move out of study area	10	88	98
Family circumstances	8	9	17
Problems with research	6	4	10
Problems with randomized design	5	-	23
Problems with services allotted	-	18	18
Health	3	5	8
Kids not interests in	3	1	4
Too much time past since last contact	3	0	3
Cultural differences	1	0	1
Stigmatization	0	1	1
Unknown	18	5	23
**Grand Total**	**159**	**189**	**366**

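### The stated power of 0.72 is planned four-group omnibus power: f is wrongly defined, month-36 loss was 36% not 25%, and the comparisons with control have no power figure

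*Protocol article*

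**What the plan says.** The Sample size section sets the conditions as "given an alpha of 0.05 and a 25% attrition rate" and proposes "300 families per group to detect any significant difference between the four groups (power was 0.99 and 0.72, respectively". The two powers belong to f = 0.25 and f = 0.10 in that order. The lower effect is described as "a small (f = 0.10) intervention effect size (mean divided by standard deviation". The section then updates enrolment: "The study randomized approximately 290 families to each group". It leaves the power at its planned value and says that there is no overall control of alpha across comparisons.

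Under Participant flow the article gives 1168 families randomized. Under Losses and exclusions after randomization it says: "At 36 months we were able to collect data from 748 families".

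The primary research question (Aim of the study) is the effect of three approaches "as compared to a control model (Existing Services), on the number of linkages that families initiate and maintain". The Primary analysis section fits a regression with a term for each of the two factors, their interaction and, where appropriate, time.

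**The concern.** A reader will use this paragraph to judge how much a null result means. Three features get in the way.

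- The gloss on f reads like a standardised mean or mean difference. Taken literally, it tells the reader that the trial had 0.72 power for a difference of 0.10 SD.
- The attrition behind the power is smaller than the 36-month loss reported later in the same article.
- The power refers to any difference among four groups, whereas the question asked is each approach against existing services.

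If 0.72 to 0.99 is taken as the power of those comparisons, or of the interaction, a null estimate could be given more weight than it can bear.

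**Working it through.** **Inputs.** Alpha 0.05, 300 per arm, 25% attrition, f = 0.25 and 0.10 (Sample size); 1:1:1:1 allocation (Study design); 1168 randomized (Participant flow); 748 with data at 36 months (Losses and exclusions). Assumptions made here: equal arms, and no gain from covariates or repeated measures.

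**1. Reproducing the stated power.** N = 4 × 300 × 0.75 = 900. The one-way F test has 3 and N − 4 degrees of freedom and noncentrality λ = N·f².

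- f = 0.10: λ = 900 × 0.01 = 9, power 0.709 (stated 0.72).
- f = 0.25: λ = 900 × 0.0625 = 56.25, power above 0.999 (stated 0.99).
- Without attrition (N = 1200), f = 0.10 gives 0.839, which does not match.

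The stated figures are therefore omnibus power after 25% loss.

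**2. Which effect size was used.** Cohen's f is the SD of the group means divided by the within-group SD. If d is the largest difference between two of four equal arms, in SD units, then f depends on the pattern of means:

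- two extreme arms, the others midway: f = d/√8
- one arm differs from the other three: f = d√3/4
- two arms differ from two: f = d/2

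If 0.10 were literally a difference of 0.10 SD, f would be 0.035, 0.043 or 0.050, and omnibus power at N = 900 would be 0.12, 0.17 or 0.21. None is near 0.72, so the calculation used Cohen's f and only the wording is wrong. Conversely, f = 0.10 means a largest difference of 0.283, 0.231 or 0.20 SD.

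**3. Month 36.** Loss = 1 − 748/1168 = 36.0%.

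- f = 0.10: λ = 748 × 0.01 = 7.48, power 0.619.
- f = 0.25: λ = 748 × 0.0625 = 46.75, power still above 0.999.
- 1168 randomized with the planned 25% loss (N = 876): 0.696 at f = 0.10. Lower enrolment thus explains about one point of the fall, and the extra attrition the rest.

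The loss counts do not agree: 414 is stated, the arms sum to 135 + 88 + 110 + 91 = 424, and 1168 − 748 = 420. Taking N as 1168 − 424 = 744 or 1168 − 414 = 754 gives 0.616 or 0.623, so the discrepancy does not matter here.

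**4. Individual contrasts.** For two arms, a two-sample t test with noncentrality d·√(n/2), two-sided 0.05, at n = 900/4 = 225 and 748/4 = 187:

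| Pattern giving f = 0.10 | Largest contrast (SD) | 225 per arm | 187 per arm |
|---|---|---|---|
| Two arms differ from two | 0.20 | 0.56 | 0.49 |
| One arm differs from three | 0.231 | 0.69 | 0.61 |
| Two extremes, two midway | 0.283 | 0.85 | 0.78 |

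These are for the largest contrast; any smaller contrast in the same pattern has less power.

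*Factorial main effect* of 0.20 SD (f = 0.10, 1 df, half the families against half): 0.85 at N = 900 and 0.78 at N = 748.

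*Interaction*, a difference of differences with standard error 2·SD/√n, at an assumed 0.20 SD (f = 0.20/4 = 0.05):

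- n = 225: 0.20/(2/15) = 1.50, and Φ(1.50 − 1.96) = 0.32
- n = 187: 0.20/(2/13.67) = 1.37, and Φ(1.37 − 1.96) = 0.28

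At f = 0.10 an interaction would be 0.40 SD and would have the same 0.85 and 0.78 as the main effect.

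**The case against.** A fair defence has five parts.

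- **The section reports a plan.** A 25% assumption that was not met is not a misstatement, and the article reports its retention openly. This stands as far as the planned 0.72 goes. A reader might infer an arithmetic error, but the figure reproduces.
- **The 36% belongs to month 36 only.** The model may use earlier visits, the hypothesis speaks of an initial increase in linkages, and no single primary time point is named. This stands. A reader might infer that the whole primary analysis fell short of its power, but the text gives no loss at 12 or 24 months. Carrying the last observation forward would keep up to 1168 families nominally (omnibus power 0.83), but it adds no month-36 information.
- **The gloss changed no number.** This stands too. A reader might infer that the wrong definition lowered the power; step 2 shows that it did not. It still tells the reader the wrong thing about the effect that could be detected.
- **The omnibus test is not foreign to the model.** Leaving the stratification covariates aside, two factors and their interaction saturate four groups, so the joint test of the three terms is the omnibus test. It would be too strong to say that 0.72 is irrelevant to the primary model. But a joint test does not answer the question for each approach. If the factors are coded 0/1 (the coding is not stated), the two factor coefficients are themselves single-approach comparisons with control.
- **Confidence intervals are promised, and a condensed article need not list every power.** The intervals will show the precision obtained. That lessens the harm, but it does not correct a wrong definition or relabel a figure already printed.

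**Conclusion.** The point holds as a correction to one paragraph. The definition of f is wrong. The stated 0.72 is planned omnibus power, and on the families observed at month 36 it is about 0.62. The comparisons that the primary question asks about have no stated power.

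A reader might infer that every comparison with control is close to a coin toss. That is only the low end (0.49) of a range that reaches 0.78 at 187 per arm, and 0.85 at 225 per arm. Nor is power below the stated figure throughout: main effects of 0.20 SD exceed it, and f = 0.25 is safe in the omnibus test at either sample size. The interaction is weak if it is 0.20 SD, but the article gives no expected size for it, so that value is an assumption.

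The equal-arm assumption is slightly kind to the comparisons with control at month 36, because Existing Services lost the most families (135, against 88 to 110 in the other arms).

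**What to change.** Rewrite the Sample size paragraph to:

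- define f as the SD of the group means divided by the within-group SD;
- label 0.99 and 0.72 as planned power of the four-group omnibus test with 900 families;
- add that with the 748 families seen at 36 months the omnibus power for f = 0.10 is about 0.62, and that f = 0.25 is unaffected;
- give power or the detectable difference for each approach against control, for the two main effects and for the interaction, stating the assumed effect in SD units and the pattern of means each time.

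The loss counts (414, 424 and 420) should be reconciled at the same time. The change needs no extra families and alters no analysis. Its cost is some rewording and a less favourable stated power.
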